| SAFETY                         |                                                   | 
 
Occurrence of adverse events: self-assessment of local and systemic reactions for 4 days after each vaccination (diary) as well as assessment by investigator during 30 minutes after each vaccination and 2 (+1) days as well as 7 (+2) days after each vaccination.
 
Occurrence of clinically significant hematological and biochemical abnormalities (hematological and biochemical analysis will be carried out at the screening visit (baseline), 7 (+2) and 21 (+5) days after each vaccination).
 
Significant reduction of health status compared to baseline (as assessed by investigator at baseline, i.e. prior to 1st vaccination, during 30 minutes after each vaccination and 21 (+5) days after each vaccination).
 
                                                                                                                                                                                                                                                                                                                                                                                                                                                                                                                                                                                                                                                                                                                                                                                                                                                                                                                                        |

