| Blood Sampling T-cell response                              | 25 mL EDTA blood, to be sent to STI within 4 hours                                     |                                                                                                                                       |                                                                                      |                                           | 25 mL EDTA blood, to be sent to STI within 4 hours |                                                                                                                                         |                                                                                      |                                           | 25 mL EDTA blood, to be sent to STI within 4 hours |                                                                                                                                           |                                                                                      |                                           | 25 mL EDTA blood, to be sent to STI within 4 hours |
| Adverse Events (Interviews and diary card)                              |                                                                                        | Baseline AE rate (prior to vaccination) after vaccination 30 minutes observation distribution diary card (self-assessment days 1 – 4) | Picture of injection site, if visible reaction. Recording of AEs check of diary card | Recording of AEs Collection of diary card |                                                    | Baseline AE rate (prior to vaccination) after vaccination 30 minutes observation distribution diary card (self-assessment days 61 – 64) | Picture of injection site, if visible reaction. Recording of AEs check of diary card | Recording of AEs Collection of diary card |                                                    | Baseline AE rate (prior to vaccination) after vaccination 30 minutes observation distribution diary card (self-assessment days 181 – 184) | Picture of injection site, if visible reaction. Recording of AEs check of diary card | Recording of AEs Collection of diary card |                                                    |

 hematology includes: hemoglobin, hematocrite, RBC count, WBC count and differential, platelets count

 blood chemistry includes ASAT/ALAT, alk. Phosphatase, creatinine, CRP

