 T-cells will not be assessed in groups PEV 301 10 µg and 302 10 µg

a Should be 9 weeks after the 1st vaccination

b must be 2 (+1) days after vaccination

c must be 7 (+2) days after vaccination

d Must be 21 (+5) days after vaccination

e Should be 26 weeks after the 1st vaccination

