## 3 Study Design

This prospective phase I, single centre, randomized, single blind, placebo controlled, dose escalating study will be conducted in 46 healthy adult volunteers. Eligible study participants will be randomized into six groups: PEV 301 10 µg (group A, n = 8) or PEV 302 10 µg (group B, n = 8) or PEV 301 50 µg (group C, n = 8) or PEV 302 50 µg (group D n = 8) or PEV 301 50 µg plus PEV 302 50 µg (group E, n = 8) or virosomes alone (group F, n = 6).

Study participants will be vaccinated three times, i.e. at days 1, 64(+2) and 183(+2) and followed-up 3 times after each vaccination. If any of the study groups does not show any immune response 3 weeks after the 2nd vaccination, no 3rd vaccination will be given to that group, i.e. the study for that group will be terminated 3 weeks after the 2nd vaccination.

Groups C & D (PEV 301 50 µg; PEV 302 50 µg) will be started 5 weeks after the 1st vaccination of groups A, B.

Group E (PEV 301 plus PEV 302) will be started 5 weeks after the 2nd vaccination of groups C and D.

Group F will be distributed and serve as a control in all groups receiving the active product.

The total duration of the study for each participant is 31 weeks, the number of visits is 13.

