### 5.2.2 Vaccinations

Volunteers will be vaccinated on days 1, 64 (57 – 66) and 183 (176 – 187) respectively. The 3rd vaccination will not be applied, if 3 weeks after the 2nd vaccination no immune response is seen.

Prior to the vaccination the baseline AE rate has to be assessed by the investigator.

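### The diary days printed for doses 2 and 3 (61–64 and 181–184) contradict the target injection days of 64 and 183 and should be counted from the actual injection

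*Protocol*

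**What the plan says.** The Adverse Events row of the Schedule of Assessments gives the diary period for each dose in study days:

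- dose 1: "distribution diary card (self-assessment days 1 – 4"
- dose 2: "diary card (self-assessment days 61 – 64"
- dose 3: "diary card (self-assessment days 181 – 184"

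The injections are placed elsewhere. Section 5.2.2 states: "Volunteers will be vaccinated on days 1, 64 (57 – 66) and 183 (176 – 187) respectively". Section 3 gives the same target days with a different allowance: "Study participants will be vaccinated three times, i.e. at days 1, 64(+2) and 183(+2". The schedule's footnotes agree on the targets: "Should be 9 weeks after the 1 st vaccination" for dose 2 and "Should be 26 weeks after the 1 st vaccination" for dose 3.

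The diary period itself is defined relative to the injection. The Synopsis, under safety criteria, has "self-assessment of local and systemic reactions for 4 days after each vaccination (diary". The Synopsis procedure text and Section 8.3.1 likewise describe a 4-day period that starts with the vaccination.

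Section 5.2 refers the site to the Schedule of Assessments for the timing of visits, vaccinations and checks.

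**The concern.** The dose 1 entry starts on the day of injection. The entries for doses 2 and 3 do not: both start before the target injection day and end on it or one day later. A site that takes the diary days from the table, as Section 5.2 directs, would be working to a period that largely misses the days it is meant to cover.

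Three features of the plan make this more than a typographical matter:

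- Local and systemic adverse events are the first safety item in Section 10.2, and the Synopsis names the diary as one source for them.
- The end of the 4-day period decides how an event is classed. Events inside it are solicited (Section 8.3.1) and are all taken as related to vaccination (Section 8.5). Events that begin after it are unsolicited (Section 8.3.2), and their causality is assessed case by case. A wrong end day can change both the label and the attribution.
- Active groups have 8 volunteers each. A few truncated or misdated reports would show in the frequency tables and in the presence/absence data for the logistic models of Section 10.6.

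**Working it through.** **Inputs.** Target days 64 and 183, with windows 57–66 and 176–187 (Section 5.2.2). Intervals of 9 and 26 weeks (schedule footnotes). Diary days 1–4, 61–64 and 181–184 (Schedule of Assessments).

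**Step 1: reproduce the target days.** With dose 1 on day 1, target day = 1 + 7 × weeks.

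- Dose 2: 1 + 7 × 9 = 64.
- Dose 3: 1 + 7 × 26 = 183.

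Both agree with Sections 3 and 5.2.2, so the targets are consistent and the diary days are the odd ones out.

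**Step 2: the dose 1 pattern.** With injection day v = 1, days 1–4 are v to v+3. Applied to the targets:

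- Dose 2: 64 to 67, against 61 to 64 printed.
- Dose 3: 183 to 186, against 181 to 184 printed.

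**Step 3: overlap with dosing on target.**

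| | Needed (v to v+3) | Printed | Needed days covered | Printed days before injection |
|---|---|---|---|---|
| Dose 2, v = 64 | 64–67 | 61–64 | 1 of 4 (64) | 3 of 4 (61, 62, 63) |
| Dose 3, v = 183 | 183–186 | 181–184 | 2 of 4 (183, 184) | 2 of 4 (181, 182) |

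Together, 3 of 8 needed days are covered and 5 of 8 printed days precede the injection.

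**Step 4: every day of the windows in Section 5.2.2.** Needed days covered, out of 4:

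| Dose 2 injection day | 57 | 58 | 59 | 60 | 61 | 62 | 63 | 64 | 65 | 66 |
|---|---|---|---|---|---|---|---|---|---|---|
| Covered | 0 | 1 | 2 | 3 | 4 | 3 | 2 | 1 | 0 | 0 |

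| Dose 3 injection day | 176 | 177 | 178 | 179 | 180 | 181 | 182 | 183 | 184 | 185 | 186 | 187 |
|---|---|---|---|---|---|---|---|---|---|---|---|---|
| Covered | 0 | 0 | 1 | 2 | 3 | 4 | 3 | 2 | 1 | 0 | 0 | 0 |

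Full coverage occurs only for an injection on exactly day 61 or day 181. With the +2 allowance of Section 3, read as printed, coverage is 1, 0, 0 for days 64, 65, 66 and 2, 1, 0 for days 183, 184, 185, so no permitted day gives a full diary.

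**Step 5: the other reading of 4 days after vaccination.** If the injection day is not counted, the needed days on target are v+1 to v+4.

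- Dose 2: 65–68, none covered by 61–64.
- Dose 3: 184–187, one covered by 181–184 (day 184).

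The mismatch does not depend on the convention. On this reading the dose 1 entry would also need changing, since days 2–5 are not days 1–4.

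**Step 6: what misdating would look like.** If a card carried the printed days and a volunteer injected on target simply used its four columns in order, entries would be dated 64 − 61 = 3 days early after dose 2 and 183 − 181 = 2 days early after dose 3. Reactions on the injection day would then carry a date before the injection.

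**The case against.** The strongest reply is that the mismatch is real but does little harm.

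- The same table cell has the card distributed after the injection and the 30-minute observation. On target, a volunteer has no dose 2 card on days 61–63. A reader might infer that pre-injection complaints would fill the post-vaccination diary; the protocol's own order of procedures rules that out.
- The Synopsis (twice) and Section 8.3.1 define the period relative to the injection. Staff handing over a card after an injection on day 65 would hardly conclude that no diary is due.
- Capture does not rest on the diary alone. There is the 30-minute observation (Section 6.4), a visit at 2 (+1) days with a check of the card, a visit at 7 (+2) days at which the investigator adds events the volunteer left out (Section 5.2.3), and recording of all adverse events for at least 30 days after each dose (Section 8.2). A reader might infer that solicited reactions would simply be missed; that does not follow.
- A reader might also say that most diary days precede the injection. That is true for dose 2 (3 of 4) and for both doses together (5 of 8), but for dose 3 it is exactly half (2 of 4).
- Scaling the loss to all 46 volunteers would assume that everyone receives both later doses on target. The protocol lets a group stop before dose 3 (Section 10.8) and does not replace dropouts (Section 5.5).
- The diary card is not in the document, so whether it carries the printed days is unknown.

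All of this stands and limits the consequence. It does not remove the error. The relative definitions show that the table is wrong, but they leave the site with two instructions, and Section 5.2 points to the wrong one. An interview up to 9 days after the injection (7 + 2) is a backstop, not a substitute for daily self-recording of reactions graded by type of pain and by diameter (Section 8.4).

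**Conclusion.** The diary days for doses 2 and 3 are wrong as written. They contradict the target days in Sections 3 and 5.2.2, the schedule's own footnotes, and the protocol's definition of the diary period. The coverage figures of 1 of 4 days (dose 2) and 2 of 4 days (dose 3) assume dosing on target, the dose 1 convention, and literal use of the printed days.

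The consequence is conditional. If the printed days are followed, or have been copied to the diary card or CRF, solicited self-reports after doses 2 and 3 could be truncated or misdated and would not be comparable with those after dose 1. The document does not support a claim that reactions will be lost outright. The item should be fixed because it sits in the table the site is told to use and bears on a primary safety measure. It changes no endpoint or analysis.

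**What to change.** In the Adverse Events row of the Schedule of Assessments, replace the fixed study days for doses 2 and 3 with days counted from the actual injection. Use one convention for all three doses and state it: either the day of vaccination and the following 3 days, which is what days 1–4 imply, or explicitly the 4 days after the day of vaccination, in which case the dose 1 entry changes too. Use the same wording in the Synopsis and Section 8.3.1, so that the line between solicited and unsolicited events is unambiguous. Because the days follow the actual injection, the correction does not depend on which of the stated injection windows applies.

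Then check that the diary card and CRF carry the same days, and use the existing card check at the 2 (+1)-day visit to confirm that the first entry matches the injection date or the day after it, according to the convention chosen.

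The cost is an edit to two table cells (three if the second convention is chosen), matching wording in the text, and a check of the card and CRF. It needs no extra visit, sample or analysis, and should be done before any volunteer receives a second dose.

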## Flow Chart

| Week of the year | Study week | Group A (8), B (8), F (2)
PEV 301/302, 10 µg | Group C (8), D (8), F (2)
PEV 301/302, 50 µg | Group E (8), F (2)
PEV 301 plus 302, 50 µg |
|------------------|------------|-------------------------------------------------|-------------------------------------------------|-----------------------------------------------|
| 45/2003          | -1         | Screening                                       |                                                 |                                               |
| 46/2003          | 1          | Vaccination 1, safety day 3                     |                                                 |                                               |
| 47/2003          | 2          | Safety interview and lab                        |                                                 |                                               |
| 48/2003          | 3          |                                                 |                                                 |                                               |
| 49/2003          | 4          | Safety lab, Immunology                          |                                                 |                                               |
| 50/2003          | 5          |                                                 | Screening                                       |                                               |
| 51/2003          | 6          |                                                 | Vaccination 1, safety day 3                     |                                               |
| 52/2003          | 7          |                                                 | Safety interview and lab                        |                                               |
| 1/2004           | 8          |                                                 |                                                 |                                               |
| 2/2004           | 9          |                                                 | Safety lab, Immunology                          |                                               |
| 3/2004           | 10         | Vaccination 2, safety day 3                     |                                                 |                                               |
| 4/2004           | 11         | Safety interview and lab                        |                                                 |                                               |
| 5/2004           | 12         |                                                 |                                                 |                                               |
| 6/2004           | 13         | Safety lab, Immunology                          |                                                 |                                               |
| 7/2004           | 14         |                                                 |                                                 |                                               |
| 8/2004           | 15         |                                                 | Vaccination 2, safety day 3                     |                                               |
| 9/2004           | 16         | Interim analysis                         | Safety interview and lab                        |                                               |
| 10/2004          | 17         |                                                 |                                                 |                                               |
| 11/2004          | 18         |                                                 | Safety lab, Immunology                          |                                               |
| 12/2004          | 19         |                                                 |                                                 | Screening                                     |
| 13/2004          | 20         |                                                 |                                                 | Vaccination 1, safety day 3                   |
| 14/2004          | 21         |                                                 |                                                 | Safety interview and lab                      |
| 15/2004          | 22         |                                                 | Interim analysis                         |                                               |
| 16/2004          | 23         |                                                 |                                                 | Safety lab, Immunology                        |
| 17/2004          | 24         |                                                 |                                                 |                                               |
| 18/2004          | 25         |                                                 |                                                 |                                               |
| 19/2004          | 26         |                                                 |                                                 |                                               |
| 20/2004          | 27         | Vaccination 3, safety day 3              |                                                 |                                               |
| 21/2004          | 28         | Safety interview and lab                 |                                                 |                                               |
| 22/2004          | 29         |                                                 |                                                 | Vaccination 2, safety day 3                   |
| 23/2004          | 30         | Safety lab, Immunology                   |                                                 | Safety interview and lab                      |
| 24/2004          | 31         |                                                 |                                                 |                                               |
| 25/2004          | 32         |                                                 | Vaccination 3, safety day 3              | Safety lab, Immunology                        |
| 26/2004          | 33         |                                                 | Safety interview and lab                 |                                               |
| 27/2004          | 34         |                                                 |                                                 |                                               |
| 28/2004          | 35         |                                                 | Safety lab, Immunology                   |                                               |
| 29/2004          | 36         |                                                 |                                                 | Interim analysis                       |
|                  |            | 10 weeks                                        |                                                 |                                               |
| 39/2004          | 46         |                                                 |                                                 | Vaccination 3, safety day 3            |
| 40/2004          | 47         |                                                 |                                                 | Safety interview and lab               |
| 41/2004          | 48         |                                                 |                                                 |                                               |
| 42/2004          | 49         |                                                 |                                                 | Safety lab, Immunology                 |

# 1 Introduction

## 1.1 Background

It is assumed that vaccines have prevented more infectious diseases than any other medical intervention, except sanitation. With currently up to 300 million affected people, malaria continues to be one of the major burdens on public health in many tropical countries. Because of the spread of drug-resistant parasites and the appearance of insecticide-resistant mosquitoes, the development of an effective vaccine against the most severe form of malaria caused by *Plasmodium falciparum* is an urgent priority. Increased travel to endemic regions and the rapid development of parasite strains resistant to current prophylactic drugs have further increased demand for efficacious products.

Since cultivation of malaria parasites on a sufficiently large scale has turned out to be not practical for mass vaccination, efforts in malaria vaccinology are currently focused on the development of a subunit vaccine. Although a number of vaccine candidate antigens have been identified, clinical trials with first vaccine formulations including recombinant viruses, DNA vaccines and adjuvanted recombinant malaria proteins, fusion proteins and synthetic peptides, have met only limited success. Since no vaccine against malaria or against another parasitic disease for use in humans is currently available, there is the belief that for the development of such vaccines innovative approaches and technologies are required. The proposed product and technology development project represents a highly innovative approach for subunit vaccine design.

